**IV. Subject Enrollment**

a) Methods of enrollment, including procedures for patient registration and/or randomization

A trained project manager will meet potential participants as a group during department meetings and verbally explain study procedures and inclusion criteria. Eligibility will be assessed based on self-report and measured height and weight. If employees from a department express interest in the study, the department will be cluster randomized into either the treadmill workstation, sit-stand workstation, or control group after completing informed consent procedures. Twenty-two volunteers will be randomly selected from each department group. In the event of insufficient volunteers in a group, the project manager will approach other departments to solicit study participation. Our recruitment target will include at least 50% women and 20% minorities, respectively. However, the study design may limit our ability to effectively recruit these two categories of participants.

b) Procedures for obtaining informed consent (including timing of consent process)

Informed consent process will be conducted during the lunch hour or a convenient time for the participant after work hours. This visit will be conducted at the participant’s physical place of work or in a private setting (if desired by the participant) on the premises of the institution. The informed consent process will be conducted by a trained project manager who will give a detailed verbal description of the study to the participants. These details will include a description of the study and complete disclosure of the various measurements and procedures that will be performed during the course of the study including the risks and discomforts as well as potential benefits associated with participation. They will then be provided with a hard copy of the informed consent form to read. Volunteers will be allowed to ask questions and clarify all their doubts during the consent process. Volunteers will be free to sign the informed consent during this visit or take up to 2 days to make a decision on study participation. They will be informed that they are free to terminate study participation at any point during the study. After they make a decision, the participants will sign the informed consent document and return it to the project manager. A copy of the signed and dated informed consent form will be given to the subject. This visit will take approximately 30 minutes to complete. If participants agree to participate, they will also complete a self-report health history questionnaire that will gather information on any pre-existing conditions related to cardio-vascular, metabolic and musculoskeletal disease. On this questionnaire, participants will also report if they are on any medications and the current dosage. In addition, participants will also complete a brief questionnaire to determine their habitual physical activity levels.

c) Treatment assignment and randomization

We will do a cluster randomization of various departments mentioned above into the control and 2 intervention groups. If employees from a department express interest in the study, the department will be cluster randomized into either the treadmill workstation, sit-stand workstation, or control group. Twenty-two volunteers will be randomly selected from each department group. In the event of insufficient volunteers in a group, the project manager will approach other departments within the hospital to solicit study participation.

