**II. Specific Aims**

The primary objective of this project is to determine the effects of decreasing sedentary behavior at work by at least 3hrs/day using treadmill (walking and standing) and sit-to-stand (standing only) workstations on the health of overweight office workers. Our central hypothesis is that decreasing sedentary behavior at work using these workstations will improve overall health in study participants.

**Aim 1:** **To** **conduct a 12-month, cluster-randomized trial with an intent-to-treat design to determine the effects of using treadmill and sit-to-stand workstations at the workplace on health variables in overweight office workers (N=66) with seated desk jobs.**

*Approach:* We will measure the following variables at baseline and/or after 3, 6, and 12 months: (a) anthropometrics (weight, waist and hip circumference) and body composition (b) blood-flow hemodynamics, (c) psychological affect, (d) job stress and (e) musculoskeletal discomfort. Blood biomarkers including fasting plasma glucose, HBA1C, and lipids will be measured at baseline and after 12 months.

All volunteers will attend a 30-min face-to-face information session at baseline on strategies and benefits of reducing workplace sedentary time and will be trained on office ergonomics to reduce musculoskeletal discomfort. We will then cluster randomize volunteers into a treadmill workstation (N=22), sit-to-stand workstation (N=22) and a control group (N=22). At an organizational level, department supervisors will be trained on the benefits of reducing workplace sedentary behavior and on strategies that encourage employees to sustain positive behavior change.

*Hypothesis*: We hypothesize that improvements in health variables for the sit-to-stand group will be significantly lower than the treadmill workstation group, but higher than the control group during follow-up.

**Aim 2:** **To compare the efficacies of treadmill and sit-to-stand workstations in decreasing workplace sedentary behavior.**

*Approach:* Based on our preliminary work using treadmill workstations, we will recommend a minimum use of 3 hours/day for the treadmill (walk: 2hrs and stand: 1hr) and sit-to-stand workstations. We will use accelerometers to measure time spent sitting, standing and in activity for 1-week at baseline and after 3, 6, 9 and 12 months.

*Hypothesis 2A*: Decrease in sedentary behavior will be greatest in the sit-to-stand group and lowest in the control group.

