**V. Study Procedures**

a) Training to use workstations and related measurements

Prior to randomization, all 66 participants will receive a 30 min face-to-face counseling session with a trained researcher on evidence-based benefits of reducing sedentary behavior and will be taught various strategies to decrease workplace sitting (e.g., taking stretch breaks, walking to a colleague’s desk instead of using the phone). We will provide individual onsite training to department-heads/supervisors in the intervention groups on the benefits and strategies to decrease sedentary behavior at work and on techniques to provide verbal encouragement to employees. Department-heads/supervisors will use these techniques to reinforce the importance of decreasing sedentary behavior at regular department meetings during the intervention. Individual participant and department-head/supervisor training sessions will be repeated after 3, 6 and 9 months.

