**Activity monitoring:** This measurement will be conducted for a period of 1 week. Participants will be asked to wear 2 small activity monitors (53 x 35 x 7 mm, weight=15 grams), one on the right thigh and the other on the torso (chest or abdomen). The device will be attached to the skin using medical grade, hypoallergenic tape or soft elastic bands. We will measure time spent at work and outside the workplace for one week using radio frequency identification technology (RFID). A thin RFID sticker tag (120 mm x 44 mm x 0.4 mm) will be wrapped around the activity monitor on the torso. This will record every time a participant enters and leaves their place of work on an RFID reader installed in the building. During this 1-week period, participants will record the times they wore and removed the monitors and the times they arrived and left their workplace. Based on the data collected using these devices, participants will be provided with retrospective feedback every 3 months on their activity behavior.

d) Procedures/surgical interventions, etc.

N/A

VI. Biostatistical Analyses

a) Specific data variables being collected during the study (e.g., data collection sheets)

Please see attached data collection forms:

1. Data collection sheet
2. Monitor log
3. Health History Questionnaire
4. Brief Block Food Questionnaire
5. Ergonomic measurements
6. Modified National Institute of Occupational Safety and Health Generic Job Stress Questionnaire
7. Positive and Negative Affect Schedule
8. Musculoskeletal Discomfort questionnaire

b) Statistical methods

Aim1: Hypothesis testing will entail an intent-to-treat two-tailed design with a nominal type I error of 0.05.  Preliminary descriptive analyses will explore observed differences in subject characteristics that may be related to study outcomes between the three groups. Variables with notable differences will be included in multivariable models. Mixed linear regression models will be used to compare differences between groups across all measurement points.  These models will include variables identified in the preliminary analyses as potential confounders.

Aim2: We will use mixed linear regression models to examine within and between-group differences in the total time spent in sedentary behavior, sitting, standing, and walking while at work and outside the workplace.

c) Power analyses

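### The top-up rule for short groups does not say how added departments are allocated and so permits non-random placement, and the protocol contradicts itself on the order of selection and randomisation

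*Protocol*

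**What the plan says.** **Allocation and selection.** Protocol IV.a takes departments as they show interest: "the department will be cluster randomized into either the treadmill workstation, sit-stand workstation, or control group after completing informed consent procedures". The next sentence is "Twenty-two volunteers will be randomly selected from each department group". I read a department group as all departments allocated to one arm, because Aim 1 and the power section (VI.c) both give 22 per arm. Section IV.c repeats the allocation rule, "If employees from a department express interest in the study, the department will be cluster randomized", but leaves out the clause that puts consent first.

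**Top-up.** IV.a continues: "In the event of insufficient volunteers in a group, the project manager will approach other departments to solicit study participation". IV.c has the same rule with a narrower source: "the project manager will approach other departments within the hospital to solicit study participation". Section III.b recruits from both a hospital and a university.

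**Order elsewhere.** Section V.a states: "Prior to randomization, all 66 participants will receive a 30 min face-to-face counseling session". Aim 1 (section II) gives the same order: volunteers attend the session at baseline and are then cluster randomised, 22 to each arm.

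**Who does what.** The project manager explains the study at department meetings (IV.a), conducts the consent process (IV.b) and approaches further departments when a group is short (IV.a, IV.c).

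**The concern.** In a cluster trial the comparison is protected by two things: each department's arm is set by chance, and its participants are identified before anyone who recruits them knows that arm. The top-up rule puts both at risk. A shortfall in a group can be seen only after departments have been allocated, so whoever acts on it knows which arm needs people. If the new department goes straight to that arm, its arm is set by need. Its staff could then decide to join knowing what they would receive, and the arms differ visibly: a treadmill workstation, a sit-to-stand workstation, or advice to take walking breaks.

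The conflict over order bears on the same safeguard. If participants are chosen after their department's arm is known, the protocol loses a simple guarantee that recruitment was blind to allocation. With few departments, one that is placed by need makes up a large part of an arm, and analysis cannot restore the randomisation it bypassed.

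**Working it through.** **1. What the top-up rule fixes and leaves open**

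| Element | IV.a | IV.c |
|---|---|---|
| Trigger | too few volunteers in a group | the same |
| Action | approach other departments | approach other departments |
| Source | not restricted | hospital only |
| Arm of the added department | not stated | not stated |

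The general rule in both sections randomises a department whose employees show interest. It makes no exception for later departments, but it does not mention them either.

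**2. Does the rule work if added departments are randomised?**

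Assume equal allocation to three arms, independently for each department. The chance that at least one of k added departments reaches the short arm is 1 − (2/3)^k:

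- k = 1: 1/3 = 33%
- k = 2: 1 − 4/9 = 56%
- k = 3: 1 − 8/27 = 70%

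On average three departments are needed to get one into the short arm. A person told to cure a shortfall therefore has a practical reason to place the department directly, and the text does not forbid it.

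**3. How much of an arm is one department?**

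The protocol gives no department sizes. They can be inferred from section VI.c, after checking that its figures hold together.

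- Inputs from VI.c: 22 per arm (66 in all), effect size 0.89, SD 3.9 kg, effective sample size 60, intra-class correlation 0.01. Two-sided 0.05 is from VI.b. Power is not given as a number; I assume 80%.
- Detectable difference: 0.89 × 3.9 = 3.47 kg, which agrees with the stated 3.5 kg.
- Number per arm: 2 × (1.960 + 0.842)² / 0.89² = 19.8, so 20 per arm and 60 in all. This agrees with the stated effective sample size.
- Design effect: 66 / 60 = 1.10.
- From 1 + (m − 1) × 0.01 = 1.10, m = 11 participants per department.
- Departments: 66 / 11 = 6, or two per arm.

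One added department of 11 is 11/22 = 50% of an arm. If departments supplied 6 each, it would be 6/22 = 27%. Both sizes are illustrations.

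**4. Order of steps, side by side**

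| Source | Stated order |
|---|---|
| Aim 1 | session for volunteers, then randomisation into three groups of 22 |
| V.a | counselling of all 66, then randomisation |
| IV.a | interest and consent, randomisation of the department, draw of 22 per group, top-up if short |
| IV.c | interest, randomisation of the department, draw of 22 per group, top-up if short |

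In Aim 1 and V.a the 66 are a known set before randomisation. In IV.a and IV.c that set is formed by arm after randomisation, and may be completed later still from departments not yet approached. As written, the two orders do not agree.

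**The case against.** **A reader might infer that the protocol fills short arms by assignment.** It does not say so. The top-up sentence is about recruitment and stops at soliciting participation. The only stated allocation rule is that an interested department is randomised, and on a plain reading this covers a department approached later. That stands: the defect is an allocation left open, not a stated non-random assignment. What remains is that the trigger is specific to an arm and that randomising serves its purpose only one time in three.

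**Consent comes before allocation.** IV.a places department randomisation after consent, so volunteers in the departments first recruited should not know their arm when they agree. This is a real safeguard. It does not help an added department whose arm has in effect been chosen before it is approached, and IV.c omits the clause.

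**The two orders could be reconciled.** If every consenting volunteer were counselled before allocation, the 66 drawn later would all have been counselled, and a random draw from a list closed before allocation is not biased in itself. So the conflict alone does not show broken randomisation. But V.a speaks of the 66, not of a larger pool, and no section says that the list is closed.

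**A reader might infer that topped-up arms would come from one institution.** The documents do not support this. IV.a has no such limit, and departments already in the arm may be from either institution. One could calculate how often unstratified allocation leaves an arm with a single institution, but that chance exists with or without a top-up rule and is no evidence against it.

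**Conclusion.** The point holds in a limited form. The top-up rule responds to a shortfall in an allocated group, leaves the arm of added departments unstated, and therefore permits whole departments to be placed without randomisation by a person who knows which arm is short and who also takes consent. Separately, Aim 1 and V.a conflict with IV.a and IV.c on whether participants are identified before randomisation, and IV.a conflicts with IV.c on where added departments may come from.

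The possible size is large for each event: about half of an arm at the 11 per department implied by VI.c, or about a quarter at 6. This rests on inferred or assumed department sizes and on reading a group as an arm. How often a top-up would be needed cannot be judged from the document. The protocol neither states that any department will be assigned by need nor shows that the randomised comparison is lost. I rate it as something that should be fixed.

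**What to change.** State one order and use it in Aim 1, IV.a, IV.c and V.a:

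1. In each department, complete consent, selection of participants, counselling and baseline measures before that department's allocation is revealed.
2. Randomise every department, including any added later and from either institution, among all three arms by the same concealed procedure, preferably stratified by institution. Say that no department is recruited for a named arm.
3. Say that arms may then differ from exactly 22.
4. Give the same source of added departments in IV.a and IV.c, consistent with the two institutions in III.b.

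The cost is a change of wording and possibly slightly unequal arms.

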**III. Subject Selection**

a) Inclusion and Exclusion criteria

1. Participants have a body mass index greater than 25 kg/m^2^
2. Do not engage in any structured physical activity for more than 2 days/week
3. Are employed in a seated desk job
4. Are free of limitations that prevent walking and standing in bouts lasting 40 to 60 min.
5. Women who are pregnant.

b) Source of subjects and Recruitment methods

Sixty-six participants will be recruited from the Massachusetts General Hospital and Northeastern University. Potential departments at Massachusetts General Hospital include The Cancer Center (protocol office and call center), Professional Billing Office, Materials Management Customer Service, Health and Information Services, Radiology Service Center, and Research Management. Departments at Northeastern University include Speech-Language Pathology Clinic, Department of Communication Sciences and Disorders, Bouve College Office of Research, The John O'Bryant African American Institute, and Northeastern University Humanities Center. These departments were previously identified as potential sites after informal communication about the study with the department heads and human resource management.

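### Departments from two institutions are randomised with no stated restriction by institution, and the top-up rule is given in two conflicting forms, so arms may by chance differ in institution

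*Protocol*

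**What the plan says.** Section III.b of the protocol sets the source population: "Sixty-six participants will be recruited from the Massachusetts General Hospital and Northeastern University". It then names candidate departments. Six are at the hospital, counting the Cancer Center once (seven if its two offices are counted separately), and five are at the university.

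Randomisation is described twice. Section IV.c says "We will do a cluster randomization of various departments mentioned above into the control and 2 intervention groups". Sections IV.a and IV.c both make the process run department by department: "If employees from a department express interest in the study, the department will be cluster randomized into either the treadmill workstation, sit-stand workstation, or control". Neither section mentions strata, blocks, matching or any other restriction, and the number of departments to be randomised is not given.

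The two sections differ on what happens when an arm is short. Section IV.a reads: "In the event of insufficient volunteers in a group, the project manager will approach other departments to solicit study participation". Section IV.c has almost the same sentence but narrows the source: "the project manager will approach other departments within the hospital to solicit study participation".

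The mixed models in Section VI.b adjust for subject characteristics that are seen to differ notably between groups. Institution is not named.

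**The concern.** When few units are randomised, an unrestricted draw often leaves the arms unlike each other on a two-level factor such as institution. Institution could plausibly matter here. Aim 2 measures sitting, standing and walking at work. Aim 1 includes job stress, and encouragement by supervisors is part of the intervention. A hospital billing office and an academic department may differ on all of these. If one arm is all hospital and another all university, the comparison between them contains no within-institution information.

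The conflicting top-up rule adds to this. Top-up is triggered by a shortfall in a particular arm, so a hospital-only source acts on that arm alone, after allocation.

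**Working it through.** **1. The plan's own figures.** Section VI.c gives 66 participants, an effective sample size of 60, an ICC of 0.01, an effect size of 0.89 and an SD of 3.9 kg.
- 0.89 × 3.9 = 3.47 kg, which agrees with the stated 3.5 kg.
- An effective 60 is 20 per arm. At two-sided 5% this gives 80.4% power for 0.89 (normal approximation; 78.3% with the t distribution). The protocol states no power; 80% is assumed.

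The sample-size arithmetic is not in dispute.

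**2. Number of departments.** The design effect is 66/60 = 1.10. Setting 1 + (m − 1) × 0.01 = 1.10 gives m = 11 people per department, so 66/11 = 6 departments, two per arm. This is an inference that assumes equal department sizes and takes 60 as exact. With 11 departments of six people, the design effect would be 1.05 and the effective size 62.9. About 6 and 11 are therefore the two working cases.

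**3. Chance that at least one arm comes from a single institution.** All allocations with the given arm sizes are taken as equally likely. The count is of ways to place the hospital departments.

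*11 named departments, 6 + 5, arms 4/4/3.* There are C(11,6) = 462 placements. Every arm is mixed when the hospital counts are:
- (2,3,1) or (3,2,1): 6 × 4 × 3 = 72 each, together 144
- (1,3,2) or (3,1,2): 4 × 4 × 3 = 48 each, together 96
- (2,2,2): 6 × 6 × 3 = 108

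The total is 348, so 462 − 348 = 114 leave a single-institution arm: 114/462 = 24.7%. In 26 of the 462 (5.6%) one arm is all hospital and another all university.

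*6 departments, 3 + 3, arms 2/2/2.* There are C(6,3) = 20 placements, of which 2 × 2 × 2 = 8 are mixed in every arm. So 12/20 = 60%, and every one of these 12 has one all-hospital arm and one all-university arm.

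| Departments (hospital + university) | Arms | Single-institution arm, unrestricted | Allocated within institution |
|---|---|---|---|
| 6 + 5 | 4/4/3 | 24.7% | 0% |
| 7 + 5 | 4/4/4 | 21.2% | 0% |
| 3 + 3 | 2/2/2 | 60% | 0% |
| 4 + 2 | 2/2/2 | 100% | cannot be avoided |

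The 4 + 2 row is no argument for stratifying: two departments cannot cover three arms. If the 11 departments were instead randomised independently, with no control of arm size, the chance is about 53% (simulation, given that no arm is empty).

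**4. Can the analysis repair it?** Take the 3 + 3 case with one arm all hospital, one all university and one mixed. Let each department mean have variance v. An additive model estimates the institution difference only from the mixed arm, with variance v + v = 2v. The adjusted contrast of the two unmixed arms has variance v/2 + v/2 + 2v = 3v. With every arm mixed by design it is v/2 + v/2 = v. Adjustment is possible, but at three times the variance and resting on one department against one.

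**5. Effect of hospital-only top-up.** If k of an arm's 22 members are hospital top-ups and the others are half hospital, the hospital share is (0.5 × (22 − k) + k)/22. For k = 4 this is 13/22 = 59%; for k = 11 it is 16.5/22 = 75%. Both values of k, and the one-half starting share, are assumptions.

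**6. Cost of a model term for institution.** At department level the residual degrees of freedom are the number of departments minus 3.
- Six departments: 3, falling to 2. The two-sided 5% critical t rises from 3.18 to 4.30, about 35%.
- Eleven departments: 8, falling to 7. The critical t rises from 2.31 to 2.36, about 3%.

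**The case against.** The protocol is silent on stratification and does not rule it out. A reader might infer that it prescribes one unstratified pool; the text does not go that far. This stands, and it limits the claim to a restriction that is not stated. But allocation is a design matter that must be settled before the first department is assigned, and both accounts of it omit institution.

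Institution may not be the right factor. Both lists contain research-administration offices, the university list includes a clinic, and every participant must hold a seated desk job. Variation within an institution may be as large as between the two. This also stands: the documents give no institution effect, so no bias in kilograms or minutes can be computed.

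The 60% rests on an inferred six departments and an assumed 3 + 3 split. That is correct, which is why the 25% from the named list comes first.

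The remedy is not free. A list of three departments balanced over three arms makes the third assignment certain once two are known, to a recruiter who can see the arms. A covariate is expensive with six departments. Both points stand and shape the fix.

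Section IV.c could be read as simply the more specific wording of Section IV.a, and top-up may never be needed. Even so, two sections of one protocol give different recruitment rules, and the narrower one is the one that can unbalance an arm.

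**Conclusion.** The point holds as a cheap improvement. Allocation has no stated restriction by institution, and Sections IV.a and IV.c contradict each other on the source of top-up departments. The chance that at least one arm comes from a single institution is 25% for the 11 named departments split 4/4/3, and 60% for six departments split 3 + 3. These figures assume near-equal numbers of departments per arm, equally likely allocations and, for the second, the inferred count and assumed split.

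A reader might infer that the results will be confounded with institution. The documents do not support that: they show a risk of chance imbalance and no institution effect. Nor do they support an inference that the institutions would use different measurement staff. Section V.b places the clinical measures in a lab, and no passage assigns staff by institution.

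**What to change.** - **Allocation (Section IV.c, repeated in IV.a).** State that departments are allocated within institution wherever each institution contributes at least three. With 6 + 5 or 3 + 3 departments, every arm can then include both. If one institution contributes fewer than three, say that this balance cannot be reached. Use a concealed list whose structure the recruiter does not know, or allocate each institution's departments in batches, so that the last assignment cannot be predicted.
- **Top-up.** Reconcile Sections IV.a and IV.c so that further departments may come from either institution and are allocated through the same lists.
- **Analysis.** Adjust for institution only if the number of departments allows. With 11 the cost is small; with about six it takes one of about three cluster-level degrees of freedom, and the choice should be made knowing that.

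The cost is a second allocation list and a few changed sentences. Batching may delay the start for departments that volunteer early. The sample size does not change.

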Sample size calculations are based on body weight change among participants (N=12) in our preliminary study.[^11^](#_ENREF_11) Our current study will have 22 participants in each of the three study arms. This will provide sufficient power to detect an effect size of 0.89 between each of the groups where the effect size = Δ/s (Δ: mean difference between two groups; s: common standard deviation). A standard deviation of 3.9 kg for weight observed in our pilot study corresponds to a mean detectable difference of 3.5 kg between groups. Although we anticipate minimal clustering within the departments at the study site, the power estimates presented above are based on an effective sample size of 60 subjects reflecting an intra-class correlation coefficient of 0.01. Comparisons between the most effective intervention and the control group will have substantially greater power reflecting larger differences in mean measurements.

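### The allocation rule fixes 22 people per arm but not the departments behind them, so an arm can rest wholly or mostly on one department and be confounded with it

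*Protocol*

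**What the plan says.** Section IV.a, and IV.c in nearly the same words, give the allocation in two steps and a back-up rule.

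- Allocation: "If employees from a department express interest in the study, the department will be cluster randomized into either the treadmill workstation, sit-stand workstation" or the control group.
- Selection: "Twenty-two volunteers will be randomly selected from each department group". With 66 participants and three arms of 22 (sections II and III.b), a department group can only mean all departments assigned to one arm.
- Back-up: "In the event of insufficient volunteers in a group, the project manager will approach other departments within the hospital to solicit study participation" (IV.c; IV.a has the same rule without the limit to the hospital).

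The protocol gives no blocking, stratification or matching of departments, no minimum number of departments per arm, and no limit on one department's share of the 22. Section III.b names eleven candidate departments, six at the hospital and five at the university, as potential sites and gives no sizes. Section VI.c bases its power statement on an "effective sample size of 60 subjects reflecting an intra-class correlation coefficient of 0.01".

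**The concern.** The only balance that the rule secures is the head count. The back-up rule also counts heads: once a department with 22 or more volunteers has filled an arm, it is never triggered.

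In an arm that is one department, the effect of the workstation and the effect of belonging to that department are the same contrast. The candidate departments differ in kind: a call centre, a billing office, a speech-language clinic and a humanities centre, across two institutions. Under section V.a the supervisors in the intervention arms are trained to encourage less sitting and to reinforce it at department meetings. The supervisor is thus part of the intervention and also a feature of the department. Job type and supervisor can plausibly act on several of the outcomes listed in section II, above all sitting time at work and job stress.

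The mixed models and covariate adjustment in section VI.b cannot separate arm from department when an arm has only one, and a later analysis plan could not either. It has to be settled at allocation, and the protocol is the document that states the allocation rule.

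**Working it through.** **Inputs.** From the protocol: 66 participants, 22 per arm (II, III.b); two-sided alpha 0.05 (VI.b); effect size 0.89, SD 3.9 kg, difference 3.5 kg, effective sample 60, ICC 0.01 (VI.c). Assumed: 80% power, since VI.c gives no figure; an ICC of 0.05 as a sensitivity value; the numbers of volunteers per department in step 5.

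**1. The plan's own figure.** With 60/3 = 20 per arm, the detectable effect is (1.960 + 0.842) × √(2/20) = 0.886 SD, or 0.886 × 3.9 = 3.46 kg. Power at 0.89 SD is 0.804 (normal approximation). The stated 0.89 and 3.5 kg are reproduced.

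**2. What that figure presupposes.** The design effect is 66/60 = 1.10 = 1 + (m − 1) × 0.01, so m = 11. That means 66/11 = 6 departments, or two of equal size per arm. Sections IV.a and IV.c contain nothing that produces this.

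**3. Effective n per arm for other make-ups.** The design effect is 1 + (Σmᵢ²/22 − 1) × ICC, and effective n = 22 / design effect. For 18 + 4, Σmᵢ²/22 = (324 + 16)/22 = 15.45.

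| Departments in the arm | Design effect, ICC 0.01 | Effective n, ICC 0.01 | Effective n, assumed ICC 0.05 |
|---|---|---|---|
| 22 | 1.210 | 18.2 | 10.7 |
| 18 + 4 | 1.145 | 19.2 | 12.8 |
| 11 + 11 | 1.100 | 20.0 | 14.7 |
| 6 + 6 + 5 + 5 | 1.045 | 21.0 | 17.9 |

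If all three arms were single departments at ICC 0.01, the detectable effect would be 0.93 SD (3.62 kg) and power at 0.89 SD 0.765. That is a small loss.

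**4. Confounding.** With k departments per arm, 3k − 3 degrees of freedom are left between departments: 3 for k = 2 and 0 for k = 1. At k = 1 the data hold no information on variation between departments within an arm, so the assumed ICC cannot be checked. On the weight scale the between-department SD is √ICC × 3.9 kg, which is 0.39 kg at ICC 0.01 and 0.87 kg at 0.05. A difference between two single-department arms then carries a department component with SD √2 × 0.39 = 0.55 kg, or √2 × 0.87 = 1.23 kg. With two equal departments per arm these become 0.39 and 0.87 kg. For weight at ICC 0.01 the component is modest against 3.5 kg. The value 0.01 rests only on the expectation in VI.c that clustering will be minimal, and VI.c gives no ICC for sitting time or job stress.

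**5. How often one department could fill or dominate an arm.** The protocol does not allow a single answer. In a simulation of 20,000 runs per setting, departments were assigned at random to arms still short of 22, and 22 people were then drawn from each arm's pool.

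| Assumed volunteers per department | Some arm wholly one department | Some arm with at least 15 of 22 from one department |
|---|---|---|
| 5 to 15 | 0% | 8% |
| 5 to 25 | 47% | 82% |
| 5 to 40 | 90% | 99% |

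Department size drives the result almost entirely.

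**The case against.** Several stronger readings are tempting, and the protocol does not support them.

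- **Departments are allocated strictly one at a time.** The conditional sentence can be read so, which would add confounding with season of enrolment. But section V.a has all 66 participants counselled before randomisation, section II places randomisation after that session, and IV.c opens with "We will do a cluster randomization of various departments mentioned above into the control and 2 intervention groups". These favour assembling departments first.
- **Imbalance is near certain.** Under independent 1:1:1 allocation of six departments, a 2-2-2 split has probability 90/729 = 12%, some arm has at most one department in 88%, and some arm has none in 189/729 = 26%. The protocol does not state that scheme, and the figures describe the position before further departments are approached. An empty arm could not persist, and a single-department arm persists only if that department has 22 eligible, consenting volunteers.
- **The largest department always supplies most of its arm.** A random draw is proportional to volunteers, so this is expected only where it holds more than half of them.
- **The power section assumes 11 per department, evenly spread.** It states neither. Both follow only by back-calculation, and with all eleven named departments the average would be 66/11 = 6.
- **Power is badly damaged.** At ICC 0.01 it is not; the larger losses need an assumed ICC such as 0.05.

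It can also be said that the method of sequence generation is commonly left to a separate plan. That is fair for block sizes. It does not cover the draw of 22 from the arm's volunteers or the back-up rule, which the protocol itself sets in terms of people only.

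**Conclusion.** The point stands in a limited form. The rule in IV.a and IV.c permits an arm made up of one department if that department has at least 22 volunteers, and an arm mostly from one department if it holds over half of the arm's volunteers. This is a statement of what the rule allows. Its probability ranges from nil to very high across plausible department sizes and cannot be fixed from the document.

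The main harm is confounding of arm with job type and supervisor, which analysis cannot repair. The loss of precision is secondary: 18.2 against 20.0 effective participants per arm at the protocol's ICC. The arithmetic in VI.c is correct, but it relies on about two equal departments per arm, and the allocation rule does not deliver that. The conclusion rests on reading a department group as all departments of one arm. Read as a single department, the rule would make every arm one department, which is worse.

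**What to change.** In sections IV.a and IV.c:

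1. Collect the interested departments first, as sections II and V.a already suggest, and randomise them together.
2. Restrict the allocation so that each arm receives the same number of departments and at least two. The explicit minimum is needed, because allocation in sets of three alone would still allow one large department per arm. Balance by institution and department size where possible.
3. Draw the 22 by near-equal quota per department, for example 11/11 or 6/6/5/5, taking more from another department of the arm only if one falls short.

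Two departments per arm means at least six, against eleven named candidates, and matches what VI.c already implies. The cost is protocol wording and a possible wait until enough departments have joined. No additional participants or workstations are needed.
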